### 2.10. Data Analysis

Statistical analysis will be carried out in IBM SPSS Statistics Version 24 (IBM Corp, New York, NY, USA). For quantitative data analysis, statistical significance will be indicated by *p* < 0.05.

Participant characteristics and survey data will be analyzed and presented using summary descriptive statistics. Statistics will include mean and standard deviation for continuous data, median and interquartile range for ordinal data and percentage and 95% confidence interval for nominal data. Comparative univariate statistics will be conducted to test for differences between control and intervention characteristics. Parametric and or non-parametric statistical tests will be used to compare the groups.

Currently the PCI has no cut-offs for the level of complexity ratings. Preliminary data will be used in a receiver operating characteristics (ROC) analysis to determine complexity rating cut-offs (categorized as low, moderate, or high) with usual care complexity rating as the criterion. Categorial level of complexity rating as a primary outcome will be compared between control and intervention groups using the Chi-square independence test.

For the first secondary outcome, modification of nursing interventions (addition or subtraction of nursing interventions), between group comparisons will be performed on distribution of intervention categories. The second secondary outcome, clinical time will be compared between the study groups using ordinal regression. Clinical time as the dependent three level categorical variable. Age and nurse’ years of community experience will be covariates, while gender, reason for referral, group allocation (intervention or control) and level of complexity rating will be factors in the regression analysis.

Qualitative data collection will be from surveys, additional information regarding nursing interventions, nurse’s feedback, field notes and observations recorded by the researcher. Audio-recorded information from focus groups will be transcribed verbatim. Inductive thematic analysis has been chosen because this will ensure that themes emerge from the data (bottom-up approach). Analysis will be conducted using Braun and Clarke’s phases which include (1) data familiarization, (2) initial code generation, (3) theme search, (4) review of themes, (5) define and name themes [46].

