### 2.2. Setting and Participants

The PCI will be trialed in a regional Victorian community nursing service, Australia, located at Bendigo Health. The community nursing service is funded by the Australian CHSP to provide traditional district nursing care to clients residing within a radius of 30 km from the service center. Clients are eligible for the service if aged 65 years old and over, have physical and cognitive function limitations, require assistance to remain living independently at home and remain engaged in their community [18]. Approximately 60 newly referred clients are seen monthly in the service by a team of 34 nurses who work a two-shift roster per day for seven days. At any one time, there are over 500 clients using the service. Community-dwelling client are referred to the service from My Aged Care, hospitals, doctors, other health practitioners, family members or themselves. Common reasons for referral are personal care, medication management, wound care, dementia support, diabetes management or continence management. Upon receiving the referral, the Intake Nurse triages the referral, collates all available information, and assigns a nurse who will visit the client for initial face-to-face assessment. A predetermined amount of time is allocated to completing the initial assessment and the associated clinical care. However, the assessment nurse may adjust this time once the assessment has been completed, for subsequent visits, based on the nurse’s assessment of care needs and nurses’ clinical judgment of level client complexity. Even though the information collected in the assessment is comprehensive, interpretation of the information is inconsistent, unstandardized and largely subjective. The decision regarding client complexity is reliant on the skill and clinical judgment by nurses.

Newly referred client assessment will form the unit of evaluation in this study. Nurses who perform these assessments will also be included as participants over the period from 1 July 2019–30 September 2020.

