### 2.5. Intervention

In this proposed study, the intervention will be made up of the PCI plus usual care assessment of complexity. The PCI measures complexity across six domains engagement in care planning, clinical need (physical and psychological), social contact, family and carers, resources, and safety. Items are scored on a Likert scale of 1 to 5 and are added to give a total score from 6 (low complexity) to 30 (high complexity). The PCI was developed in a community nursing service caring for adults in Wales and validated using Rasch analysis to determine the probability of an item indicating complexity. Each item in the PCI was determined to be a good fit to determine complexity.

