### 2.6. Sample Size

Initial data will be used to conduct a post hoc sample size calculation. Up to *n* = 34 (all) nurses in the community nursing service will make up the nurse participant sample. These are nurses making up the team who would normally be available to conduct assessments on referred clients. Based on the number of new referrals expected over three-month period, a convenience sample of up to *n* = 180 patient assessments (90 per group) will be targeted and up to *n* = 27 (all) nurses in the service will make up the nurse participant sample. Due to the pilot nature of the study, formal sample size calculation is not critical. Pilot studies by their nature are not aimed at establishing a definitive effect, however a rationale for sample size basis such as described above is deemed sufficient [44,45].

Using our early pilot data, post hoc sample size calculation was performed based on the proportions of the level of complexity rating in the ImPaCt study. A minimum total sample *n* = 138 patient assessments, i.e., 69 per group (Figure 1) will be required in definitive trial to detect a significant difference in proportions relating to a high level of complexity rating between the control (23.1%) vs. intervention (5.7%), odds ratio = 4.97, power = 0.8 and *p* < 0.05.

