### 2.8. Study Procedures

Prior to participating in the study, nurses will be briefed about the project and provided with a brief education about using the PCI. This will ensure that each nurse receives the same information. No further instruction will be provided on the PCI which will remove the risk of researcher influence.

Each nurse will be allocated a code that will be used for each assessment they complete. This code will not identify the nurse and will be provided by an independent person, it will be used for analysis purposes only. The code will be allocated to each nurse involved using a sealed envelope system at the commencement of the project and on consent. This will ensure that data related to the learning effect can be analyzed.

The nurses will be provided with an introduction to the PCI and asked to complete the nurse pre RCT survey (File S1 in Supplementary). On completion of data collection, the nurse will be asked to complete the post RCT survey (File S2 in Supplementary).

As described earlier in local context, the Intake Nurse is responsible for allocating new referrals for assessment to nurses through a daily list. They will in addition provide the sealed group allocation envelope to the nurse on return to the office. On return, the nurse will open the envelope to determine the group type. The nurse will then retrieve the appropriate group envelope containing the required study documents. The control group envelope will contain the nurse information and consent (File S3 in Supplementary) and the nurse assessment survey 1 (File S4 in Supplementary). The intervention group envelope will include, in addition to the above, the PCI (File S5 in Supplementary) and the nurse assessment survey 2 (File S6 in Supplementary).

The control group: an assessment will be completed following the current usual process. The nurse conducting the assessment will be asked to rate and justify the client’s complexity using judgment as usual and will not be prompted in any way.

The intervention group: an assessment, documentation and data collection will be carried out as for the control group with exception of the inclusion of survey 2. Once client assessment has been completed and away from client interaction, the nurse then completes the PCI and nurse survey 2 which comprises of questions pertaining to the PCI. The researcher will not lead or prompt the nurses.

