### 2.9. Outcomes

The primary outcome of the RCT component is client complexity rating (low, moderate, or high) as measured using the PCI (intervention) or usual assessment nurse judgment alone (control).

The first secondary outcome is the addition of nursing care interventions after initial assessment. These are the required interventions for the client based on the assessment outcome and the detected level of client complexity. The nursing care interventions will be categorized as medication support, wound care, referrals and liaison and others. The second secondary outcome is the nursing care time added in minutes. This is the additional time that may be allocated to the delivery of the nursing care interventions for the clients following assessment and detected level of client complexity. 

Data will be collected using baseline and follow up surveys (File S1 and S2 in Supplementary) completed by participating nurses allocated to the intervention group pre- and post-PCI use. The survey will be administered electronically or via paper form. It will be supplemented with field notes and observations recorded by the researcher throughout the study. Any focus groups or interviews conducted will be recorded for transcription.

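### The primary test compares PCI categories, cut by ROC to agree with usual-care ratings, against those same usual-care ratings, so its result depends on the cut-off rule and cannot show better detection

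*Protocol article*

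**What the plan says.** All references are to the protocol article.

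- **Outcome (section 2.9).** The primary outcome is a low, moderate or high complexity rating, "as measured using the PCI (intervention) or usual assessment nurse judgment alone (control").
- **PCI scale (section 2.5).** The instrument gives a "total score from 6 (low complexity) to 30 (high complexity"). Section 2.10 adds: "Currently the PCI has no cut-offs for the level of complexity ratings".
- **Cut-offs (section 2.10).** "Preliminary data will be used in a receiver operating characteristics (ROC) analysis", in order to "determine complexity rating cut-offs (categorized as low, moderate, or high) with usual care complexity rating as the criterion". No rule for choosing the point on the ROC curve is stated. The resulting categories go into a between-arm chi-square test at p < 0.05.
- **Status of the criterion (section 2.2).** Of the usual assessment, the article says that "interpretation of the information is inconsistent, unstandardized and largely subjective".
- **Aim (section 1.5).** The primary null hypothesis is that adding the PCI has no effect on nurses' detection of complexity compared with usual assessment alone.
- **Order of data collection (section 2.8).** In the intervention arm "an assessment, documentation and data collection will be carried out as for the control group with exception of the inclusion of survey 2". The PCI and survey 2 are completed after that assessment, away from the client.
- **Early data (section 2.6).** A sample size for a definitive trial is "based on the proportions of the level of complexity rating in the ImPaCt study", with 23.1% rated high in control and 5.7% in intervention.

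**The concern.** ROC analysis treats its criterion as the truth, so each disagreement between the PCI and the nurse counts as a PCI error. A tool tuned in this way to agree with usual judgment cannot then be shown to detect complexity that usual judgment misses. The article names no other reference for true complexity.

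The second problem is that the arms do not share a measure. The control arm's category shares come from nurses' judgment. The intervention arm's shares come from a score cut at points still to be chosen. Common ROC rules balance sensitivity and specificity and do not aim to reproduce category frequencies. The shares can therefore differ between arms when nothing about detection differs.

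At stake is the interpretation of the primary result. A significant chi-square could arise from the cut-off rule alone, and a null result could arise from a rule that makes the PCI mimic the nurses.

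**Working it through.** **1. The plan's own figure.** Section 2.6 gives 23.1% vs 5.7% rated high, odds ratio 4.97, power 0.8 and 69 per group.

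- Odds ratio: (0.231/0.769) / (0.057/0.943) = 0.3004/0.0604 = 4.97. It reproduces.
- Two-sided Fisher exact power at alpha 0.05, by full enumeration: 0.795 at 68 per arm and 0.802 at 69 per arm. So 69 per arm, 138 in total, reproduces.

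The arithmetic is not at fault. The question is what the 5.7% measures.

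**2. How far the share rated high depends on the cut-off.** Assume PCI totals are roughly normal with mean 15 and SD 4 (not in the article). For cut-off c, the share rated high is 1 − Φ((c − 0.5 − 15)/4).

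| Cut-off | z | Rated high |
|---|---|---|
| 17 | 0.375 | 35.4% |
| 18 | 0.625 | 26.6% |
| 19 | 0.875 | 19.1% |
| 21 | 1.375 | 8.5% |
| 22 | 1.625 | 5.2% |

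With the same clients and the same scores, moving the cut-off by 3 to 4 points on the 6-30 scale changes the share from about 23% to about 6%. That is the whole contrast in section 2.6. If the 5.7% is the PCI-based rating that section 2.9 defines, it depends on the cut-off to this extent.

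**3. Null simulation of the primary test.** Clients and nurse judgment are identical in both arms.

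- From the article: 69 per arm, 23.1% rated high by nurses, three-level chi-square, alpha 0.05.
- Assumed: 35% rated low; PCI mean 15, SD 4; correlation between the PCI and the judgment underlying the nurse's rating of 0.3 to 0.9; two cut-offs (high vs the rest, low vs the rest), chosen either by the Youden index or to match the nurses' frequencies.

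There were 500 runs per setting with cut-offs derived in the same 69 intervention assessments, and 300 with cut-offs from a separate sample of 70.

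| Correlation | Youden, same data | Mean PCI high | Youden, separate 70 | Matched, same data | Matched, separate 70 |
|---|---|---|---|---|---|
| 0.3 | 86% | 44% | 87% | 9% | 18% |
| 0.5 | 77% | 42% | 80% | 8% | 18% |
| 0.7 | 70% | 38% | 67% | 9% | 22% |
| 0.9 | 41% | 31% | 50% | 9% | 10% |

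All columns except mean PCI high show the rejection rate of a nominal 5% test. With 10% rated high and 45% low by nurses, the same-data figures were 44% to 90% (Youden) and 6% to 9% (matched).

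At the 90 per arm targeted in section 2.6, Youden cut-offs gave about 65% to 88% at correlations 0.4 to 0.8 and about 47% at 0.9. A rougher frequency match gave about 14%. Comparing nurse ratings with nurse ratings in the two arms gave 3% to 7%, close to nominal.

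**4. Which feature drives it.** With Youden cut-offs, calibrating in a separate sample leaves the rejection rate about as high (50% to 89% over both sets of nurse frequencies, against 41% to 90%). Reuse of data is therefore not the main cause. The causes are the unlike instruments and the choice of criterion.

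**The case against.** Several points on the other side carry weight.

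- **Reuse of trial data.** A reader might infer that the assessments that set the cut-offs are then tested against control. Section 2.10 says only that the data are preliminary. Section 2.6 places early pilot data within ImPaCt, and section 2.8 appears to yield both ratings only in the intervention arm, so the reading is likely. It is not stated, and step 4 shows that it matters little.
- **The size rests on an unstated rule.** The article does not specify Youden. A reader might take 65% to 88% as the false-positive rate of this trial. The documents do not support a single figure; the range runs from near nominal to about 90%. That dependence on an unstated rule is itself the problem.
- **Direction.** The simulated PCI share rated high exceeds control, whereas section 2.6 reports fewer in intervention (5.7% vs 23.1%). With Youden cut-offs at 90 per arm, a share of 6% or less arose in only 0% to 1.5% of null trials. The simulation shows that the test is uninterpretable and does not explain the early data.
- **Matched cut-offs.** A reader might say that matching makes the difference exactly zero. It does so only in expectation, because the nurse ratings being matched come from different clients than the control ratings.
- **Pilot status.** Section 2.6 says pilot studies do not aim at a definitive effect. This lowers the stakes, but section 1.5 states a primary null hypothesis and section 2.10 tests it at p < 0.05.

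**Conclusion.** The concern holds in this form: the ROC criterion is the comparator itself, each arm is measured with a different instrument, and so the primary chi-square reflects the cut-off rule and cannot show that the PCI improves detection. With no true difference, a nominal 5% test rejects in about 40% to 90% of trials under Youden cut-offs. It rejects in about 6% to 15% under cut-offs matched to nurse frequencies, or up to 22% if the matching is done in a separate small sample. Matching brings the rate down only by pushing the arms towards agreement, so it does not rescue the test. These figures assume a rule, a correlation and a PCI distribution that the article does not give. The logical point needs none of them. The primary analysis should be changed before it is run.

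**What to change.** 1. Remove ROC-cut PCI categories from the between-arm primary test.
2. Make the primary outcome the nurse's final low, moderate or high rating, on the same scale in both arms, and compare it by chi-square. In the intervention arm, record it after the PCI is completed. The rating now common to both arms appears, from section 2.8, to precede the PCI, so comparing that one could not show any effect of the PCI.
3. Report the PCI as its 6-30 total, with its association with the nurse's pre-PCI rating in the intervention arm. Keep any ROC cut-offs exploratory. Deriving them in separate clients is not enough by itself (step 4 of the working). Added care time or interventions are not an independent criterion either, since section 2.9 makes them follow from the detected complexity.
4. State that a difference in ratings shows a change in rating and not better accuracy, because no independent reference standard is named.
5. State in section 2.6 that the 5.7%, if PCI-based, depends on the cut-off and should not size the definitive trial.

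The cost is analysis wording and, if survey 2 (not shown) does not already capture it, one post-PCI rating item.

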### 1.5. Aim and Objectives

The Improving Detection of Patient Complexity in the Community (ImPaCt) is a trial of the PCI within the community nursing service to improve detection of client complexity in regional Victoria. The primary objective is to explore whether adding the PCI to the usual assessment process could enhance the detection of the complexity of clients and support the clinical judgment. The secondary objective is to explore whether using the PCI derived client complexity could facilitate appropriate resource allocation; these resources being the time allocated to providing clinical care to the complex client or referrals completed to support the client. The study will also explore issues around the feasibility and acceptability of the PCI in community nursing.

This study aims to answer the question “Does the PCI in addition to usual assessment, enhance nurses’ detection of complexity and delivery of appropriate allocation of care for community dwelling patients aged 65 and over?”.

The primary null hypothesis is the addition of the PCI has no effect on nurses’ detection of patient complexity compared to usual assessment alone. The secondary null hypothesis is the addition of the PCI does not enhance the allocation of appropriate resources according to the client’s complexity. 

Ethical approval has been provided by the researchers’ employer and the supporting University reference number (blinded). The trial has been registered with the Australian and New Zealand Clinical Trials Registry (blinded).

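### Sections 2.9 and 2.10 disagree on both secondary outcomes: added interventions are analysed as a spread over categories that includes subtractions, and added minutes as a three-level clinical time.

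*Protocol article*

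**What the plan says.** **First secondary outcome.** Section 2.9 states: "The first secondary outcome is the addition of nursing care interventions after initial assessment". It then lists types: "The nursing care interventions will be categorized as medication support, wound care, referrals and liaison and others". No level for clients with nothing added is listed. Section 2.10 calls the same outcome "modification of nursing interventions (addition or subtraction of nursing interventions" and states that "between group comparisons will be performed on distribution of intervention categories". It names neither the test nor the unit of analysis.

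**Second secondary outcome.** Section 2.9 states: "The second secondary outcome is the nursing care time added in minutes". Section 2.10 states: "The second secondary outcome, clinical time will be compared between the study groups using ordinal regression", and then: "Clinical time as the dependent three level categorical variable". The levels are not described.

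**The hypothesis these outcomes serve.** Section 1.5 states: "The secondary null hypothesis is the addition of the PCI does not enhance the allocation of appropriate resources according to the client’s complexity". The same section explains resources as time allocated to care, or referrals completed.

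**The concern.** These two outcomes carry the whole secondary hypothesis. For each, the quantity to be compared is not the quantity defined.

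For interventions there are two differences. Subtractions enter an outcome that was defined by additions alone. The comparison is also on type, whereas the definition asks whether, or how much, was added. A result of no difference in type could sit beside a real difference in the amount of care added.

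For time, both the scale and the label change. The label matters because Section 2.2 describes a predetermined time that the nurse may adjust after assessment. Total clinical time and added time are therefore different variables. Reducing minutes to three levels also discards ordering that the chosen ordinal method could use.

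**Working it through.** The plan gives no sample size, power, mean, spread or cut-point for either secondary outcome, so there is no figure of its own to reproduce here. The 138 assessments in Section 2.6 concern the primary outcome. What follows is illustration under stated assumptions, with the targeted 90 per group (Section 2.6).

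**1. Does a comparison of mix respond to more interventions?**

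Suppose interventions are pooled over clients into a table of arm by type. A chi-square test compares each count with (arm total) × (overall share of that type). If both arms have the same shares, the expected table fits whatever the arm totals are. A pure increase in volume therefore leaves the test at its type I error rate.

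Simulation: 3,000 trials, Poisson counts per client, control mean 1.0, the same mix of 30/25/30/15% in both arms, two-sided 5% level.

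| PCI-arm mean per client | Mix test rejects | Rank test on number added rejects |
|---|---|---|
| 1.0 | 4.8% | 5.1% |
| 1.5 | 4.8% | 83.4% |
| 2.0 | 4.9% | over 99% |

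Types were drawn independently here. If one client's interventions are correlated, pooling would also disturb the 5% error rate.

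The result depends on there being no level for nothing added. Under the same Poisson assumption, the share of clients with none is e^(−1) = 0.368 at mean 1.0 and e^(−2) = 0.135 at mean 2.0. A per-client comparison with such a level would see that difference.

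**2. What do three levels cost for time?**

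For small effects under proportional odds, the information kept by levels with shares p, relative to an outcome without ties, is 1 − Σp³.

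- Equal thirds: 1 − 3 × (1/3)³ = 0.889, a loss of 11%.
- 60/30/10: 1 − (0.216 + 0.027 + 0.001) = 0.756, a loss of 24%.
- 70/20/10: 1 − (0.343 + 0.008 + 0.001) = 0.648, a loss of 35%.

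That comparator has no ties. Suppose instead that the largest level (one of the thirds in the first case) is clients with exactly zero added time. Those ties remain however minutes are analysed, so uncut minutes reach at most 1 − p₀³, where p₀ is the share at zero.

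| Split | Three levels | Uncut, at most | Kept | Lost, of 180 |
|---|---|---|---|---|
| Equal thirds | 0.889 | 1 − 0.037 = 0.963 | 92.3% | about 14 |
| 60/30/10 | 0.756 | 1 − 0.216 = 0.784 | 96.4% | about 6 |
| 70/20/10 | 0.648 | 1 − 0.343 = 0.657 | 98.6% | 2 to 3 |

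Without ties, the same splits would cost 20, 44 and 63 of 180. The skewed splits that look worst without ties cost least when their largest level is zero.

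Against a different benchmark, a normal shift in minutes analysed as minutes, three levels kept 79% at tertiles and between 52% and 81% over the cuts tried. That benchmark fits skewed data with many zeros poorly and is not the plan's own method, so it is not carried into the conclusion.

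**The case against.** **The sentence on categories is condensed.** Section 2.2 makes the client assessment the unit of evaluation, which points away from pooling. If each category were compared per client, or a level for none were included, the test would respond to a doubling. This stands: the insensitivity shown above belongs to one reading. But the text states no other reading, and the four types it lists include no such level.

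**More is not the same as appropriate.** Section 1.5 asks about appropriate allocation, and Section 3 expects fewer duplicated referrals. Type and subtractions are then relevant. This is a good reason to report both, but not to fold them into an outcome defined as additions.

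**A few ordered levels can be sensible** for skewed minutes with many zeros, and the loss may then be small. This stands, as the second table shows. Ordinal regression itself is not in question.

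**Stronger readings that the documents do not support.** A reader might infer that the first analysis has no power at all. That holds only for pooled interventions with an identical mix in both arms. A reader might infer that three levels throw away 44 or 63 of 180 assessments. That assumes minutes without ties, and the documents give neither splits nor cut-points. A reader might also take it as settled that minutes are recorded and then cut. Section 2.9 implies recording in minutes, but the nurse assessment surveys are not shown and may use bands.

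Naming the test, the unit and the cut-points can be left to a fuller plan. The contradiction between two sections of the same article cannot.

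**Conclusion.** The two sections contradict each other on both secondary outcomes, and nothing elsewhere in the protocol reconciles them. That conclusion rests on the text alone.

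The consequences are conditional. If the first analysis compares the mix of the four types, it does not respond to a proportional increase in added interventions, and pooling would breach independence. For time, three levels can only lose information. The illustrative loss is about 1% to 8% with the lowest level at zero, and about 11% to 35% with essentially untied minutes.

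The outcomes are secondary and Section 2.6 describes the study as a pilot, so this does not threaten the trial. It does limit what can be concluded about resource allocation, and it is cheap to repair.

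**What to change.** - Use one definition of each secondary outcome in Sections 2.9 and 2.10.
- **Interventions:** with the client assessment as the unit, compare any intervention added (yes/no) and number added between groups. Report subtractions separately. Give per-category rates as description.
- **Time:** fit the planned ordinal regression to added minutes as recorded, grouping only sparse values. Keep the three-level version for display.
- If time is captured only in bands, correct the definition in Section 2.9 to those bands instead.

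Cost: a change of analysis wording and slightly more analysis work, with no additional clients. If minutes are recorded as Section 2.9 implies, no new data are needed. The ordinal model may have sparse levels with up to 180 assessments and the listed factors and covariates, hence the allowance for grouping.

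### The care-time regression adjusts the group effect for the complexity rating, a post-allocation outcome on the intended causal path, so the group coefficient does not estimate the effect of adding the PCI

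*Protocol article*

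**What the plan says.** **The model.** Section 2.10 of the protocol article sets out the analysis of the second secondary outcome: "The second secondary outcome, clinical time will be compared between the study groups using ordinal regression". The response is ordered: "Clinical time as the dependent three level categorical variable". Age and the nurse's years of community experience are covariates. Gender and reason for referral are factors, and then "group allocation (intervention or control) and level of complexity rating will be factors in the regression analysis". No comparison of care time without the rating is stated.

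**The rating.** Section 2.9 defines the primary outcome as "client complexity rating (low, moderate, or high) as measured using the PCI (intervention) or usual assessment nurse judgment alone (control"). Section 2.10 uses the same term for it: "Categorial level of complexity rating as a primary outcome will be compared between control and intervention groups using the Chi-square independence test".

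**The link from rating to time.** Section 2.9 says that care time is added "for the clients following assessment and detected level of client complexity". In section 1.5 the secondary objective is whether complexity derived from the PCI helps to allocate resources appropriately. The secondary null hypothesis there is that "the addition of the PCI does not enhance the allocation of appropriate resources", where what is appropriate depends on how complex the client is.

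**The concern.** Randomisation supports a comparison of the arms as allocated. It does not support a comparison within levels of something that the allocation itself may have changed. Two separate problems follow from entering the rating beside group.

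- **Removal.** If the PCI changes the rating and the rating changes the time allotted, holding the rating fixed takes out the effect that the secondary objective asks about.
- **Creation.** The same label is produced by different methods in the two arms. If one arm uses the high label more sparingly, clients with that label differ in true need between arms, although need is balanced overall. A group difference in time can then appear within rating levels when the PCI has done nothing to time.

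At stake is the only stated group test of care time. It could miss a real change in resource allocation, or report one that is not there.

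**Working it through.** **1. The plan's own figures.** Section 2.6 gives 23.1% (control) and 5.7% (intervention) rated high, an odds ratio of 4.97, power 0.8 and 69 per group.

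- Odds ratio: (0.231/0.769) / (0.057/0.943) = 0.3004/0.0604 = 4.97. Reproduced.
- Exact power of Fisher's two-sided test at 0.05: 0.7945 with 68 per group and 0.8021 with 69. The 69 per group (138 in total) is reproduced, and the present point does not affect it.

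**2. Why one rating level holds different clients in each arm.** Assume that true need is standard normal in both arms and that each arm labels its neediest fraction p as high. With cut-point c, mean need is φ(c)/p among those rated high and −φ(c)/(1−p) among the rest.

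| Arm | p | c | φ(c) | Mean need, high | Mean need, not high |
|---|---|---|---|---|---|
| Control | 0.231 | 0.736 | 0.304 | 1.32 | −0.40 |
| Intervention | 0.057 | 1.580 | 0.114 | 2.01 | −0.12 |

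The overall mean is 0 in both arms. Within a level, intervention clients have greater need: by 2.01 − 1.32 = 0.69 SD among those rated high, and by −0.12 + 0.40, about 0.27 SD, among the rest. How the rest divide into low and moderate can strengthen or offset this, and the documents do not give that split.

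**3. Simulated group odds ratio for care time.** Inputs from the documents: 23.1% and 5.7% rated high, a three-level time variable, and 180 assessments (90 per group, section 2.6). Assumptions: the share rated low; a rating with reliability 0.8 for need; and the slope β. Time is a latent logistic variable cut into three levels.

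- *Null:* time depends on true need only (β per SD of need), with no group effect.
- *Full mediation:* time depends on the recorded rating only (β per rating level).

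Each data set was fitted by a proportional-odds model with group alone, then with group plus rating. The other planned covariates were left out. Odds ratios come from n = 40,000 and rejection rates from 200 trials of n = 180.

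| Low share, control / intervention | Scenario | β | OR without rating | OR with rating | Rejection without | Rejection with |
|---|---|---|---|---|---|---|
| 40% / 60% | null | 1.0 | 1.01 | 1.48 | 3.0% | 20.5% |
| 40% / 60% | null | 1.5 | 1.02 | 1.77 | 7.0% | 47.0% |
| 40% / 60% | mediated | 1.0 | 0.68 | 0.96 | 24.5% | 8.0% |
| 40% / 60% | mediated | 1.5 | 0.63 | 1.01 | 47.5% | 7.0% |
| 40% / 40% | null | 1.0 | 1.00 | 1.18 | 3.5% | 8.0% |
| 40% / 40% | null | 1.5 | 1.01 | 1.31 | 6.5% | 14.0% |
| 40% / 40% | mediated | 1.0 | 0.82 | 0.97 | 10.5% | 7.0% |
| 40% / 40% | mediated | 1.5 | 0.83 | 1.02 | 12.5% | 6.0% |

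With 200 trials, the standard error of a 5% rejection rate is √(0.05 × 0.95/200) = 1.5 percentage points.

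**4. Sensitivity of the false effect.** A separate null run (n = 60,000, slopes 0.3 to 1.5 log-odds per SD of need) gave these odds ratios with the rating in the model:

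- low share 35% / 45%: 1.08 to 1.45;
- low share 40% / 40%: 1.03 to 1.26;
- low share 45% / 35%: 1.01 to 1.07.

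A further run (n = 40,000) over a range of splits and slopes gave about 1.0 to 1.7 under the null. It took fully mediated odds ratios of 0.63 to 0.97 to about 1.0.

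**The case against.** **The hypothesis may be about time at a given complexity.** The secondary null in section 1.5 refers to the client's complexity, which may be why the rating was entered. That is a fair question, but a rating defined differently by arm cannot answer it. A reader might go further and infer that the model must contain a group-by-complexity interaction, using a nurse rating taken before allocation. The documents do not support that. Section 1.5 specifies no interaction. In section 2.8 the nurse opens the allocation first and only then retrieves the group envelope holding the survey, so no rating before allocation is described.

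**A common nurse rating may exist.** Section 2.8 says that data collection in the intervention arm follows the control arm, so nurse judgment may be recorded in both. If that rating entered the model, most of the false-effect argument would fall away. But section 2.10 does not say so, and sections 2.9 and 2.10 use the term for the arm-specific outcome. The arm-specific reading is the likelier one, not a certain one.

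**Other tests are mentioned.** Section 2.10 also promises parametric or non-parametric group comparisons. That sentence stands in the paragraph on participant characteristics and survey data and does not name care time.

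**The size is not fixed by the documents.** This stands. With a low share of 45% / 35% the false effect nearly vanishes. A reader might infer that adjustment always erases the effect, or always inflates false positives. Neither follows: removal is complete only under full mediation, which no passage asserts, and the false effect depends on the low/moderate split and on how strongly time follows need.

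**It is a secondary outcome in a pilot.** This also stands, and it lowers the severity. It does not remove the point, because section 1.5 states a formal secondary null hypothesis and section 2.10 sets significance at p < 0.05.

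**Conclusion.** The concern holds. The only stated group comparison of care time conditions on the primary outcome, which arises after allocation, is defined differently by arm, and lies on the path from the PCI to time. Its group coefficient does not estimate the effect of adding the PCI.

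Across the assumptions tried, a true null odds ratio of 1.0 becomes anything from about 1.0 to about 1.8 (largest single value 1.77), and a fully mediated odds ratio of 0.63 to 0.97 becomes about 1.0. If the effect runs only partly through the rating, only part of it is lost. The figures rest on the protocol's 23.1% and 5.7%, together with assumed low shares, rating reliability and time slopes, so they show direction and plausible scale and are not properties of this trial.

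Severity: should be fixed. The primary chi-square comparison and the sample size are unaffected.

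**What to change.** In section 2.10, remove level of complexity rating from the ordinal regression that tests group. Keep group allocation and the variables already set when the envelope is opened: age, gender, reason for referral and the nurse's years of community experience. If a model containing the rating is still wanted, label it exploratory and say which rating it uses in each arm.

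The cost is one line of analysis wording, with no new data and no change to procedures. The group test then addresses the total effect of adding the PCI on care time, not the difference in time at a given complexity level; that second question passes to the exploratory model.
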